## Abstract

**Background:**

Prevalence of hearing loss increases with age. Its estimated prevalence is 40–50 % in people over 75 years of age. Recent studies agree that declinein hearing threshold contribute to deterioration in sociality, sensitivity, cognition, and quality of life for elderly subjects.

The aim of the study presented in this paper is to verify whether or not rehabilitation using first time applied Hearing Aids (HA) in a cohort of old people with hearing impairment improves both speech perception in a noisy environment over time and the overall health-related quality of life.

**Methods:**

The monocentric, prospective, repeated measurements, single-subject, clinical observational study is to recruit 100 older adults, first-time HA recipients (≥ 65 years).The evaluation protocol is designed to analyze changes in specific measurement tools a year after the first HA usage in comparison with the evaluation before HA fitting.

Evaluations will consist of multiparametric details collected through self-report questionnaires completed by the recipients and a series of commonly used audiometric measures and geriatric assessment tools. The primary indicator of changes in speech perception in noise to be used is the Italian version of Oldenburg Satz (OLSA) test whereas the indicator of changes in overall quality of life will be the Assessment of Quality of Life (AQoL) and Hearing Handicap Inventory for the Elderly (HHIE) questionnaires. The Montreal Cognitive Assessment (MoCA) will help in screening the cognitive state of the subjects.

**Discussion:**

The protocol is designed to make use of measurement tools that have already been applied to the hearing-impaired population in order to compare the effects of HA rehabilitation in the older adults immediately before first HA usage (Pre) and after 1 year of experience (Post). This broad approach will lead to a greater understanding of how useful hearing influences the quality of life in older individuals, and therefore improves potentials for healthy aging. The data is to be analyzed by using an intrasubject endpoint comparison. Outcomes will be described and analyzed in detail.

**Trial registration:**

This research was retrospectively registered underno. NCT04333043at ClinicalTrials.gov (http://www.clinicaltrials.gov/) on the 26 March 2020. This research has been registered with the Ethics Committee of the Area Vasta Emilia Nord under number 104, date of approval 17/07/2017.

## Background

Hearing loss is one of the most common disabilities in the world. Prevalence of this disease increases with age and its estimated prevalence is 40–50 % in people older than 75 years [1].

The term presbyacusis refers to decreased hearing sensitivity in older adults subjects. Nevertheless, this term has a broader meaning including all types of hearing loss that occur in the older adults. Presbyacusis also involves genetic age-related cumulative effects and potential secondary injuries to the auditory system (noise-induced hearing loss, ototoxicity, etc.).

Presbyacusis is the main cause of stable hearing loss and the most common disablingdisease in the older adults. [2].

Presbycusis is characterized by a bilateral symmetrical neurosensorial hearing loss that initially involves high frequencies and secondarily medium and low frequencies. Auditory threshold modifications are related to variations in detection, localization and speech discrimination especially in noisy environments [3, 4]. These variations deteriorate sociality, sensitivity, cognition, and quality of life of the subject [5–7].

However, cognitive abilities can benefit from the hearing-impaired subject using a hearing aid (HA). It is clear that hearing loss and cognitive abilities are linked and influence each other [8, 9].

Periodic monitoring of the hearing threshold is essential in early identification of communication disability or handicap, and the initiation of early treatment.

Since presbycusis is a multifactorial disease, the decline of the auditory threshold can be reduced by limited noise exposure, medical treatment in case of systemic or ear diseases or, in most cases, by using a HA [10–12].

Various studies have shown that HA improve quality of life (QoL) and cognitive functions in patients with presbycusis [8, 13–15]. Compared to patients with untreated hearing loss, patients with HA show improvements in social and emotional scores, communication and cognition skills, and do not suffer so much from depression [16].

In most studies, HA benefit is investigated using traditional clinical audiometric tests or self-assessed outcomes [17]. Only a few studies use multiparametric experimental protocols that explore both audiometric and cognitive skills improvement in older hearing-impaired subjects with HA [7].

In a recent study, Tognola et al. investigated HA benefit in the older adults using complete multi-parametric protocol. This study shows a significant correlation between auditory outcomes, hearing impairment, and cognition but it examined subjects once (a year after the first fitting of HA) and it did not investigate the role played by HA use in maintaining long-term health outcomes. [18].

The present paper describes the first application of the protocol design of a monocentric prospective longitudinal study in a large cohort of older adults with HA. Its unique features include severaltests that include evaluation of hearing aid benefit in a noisy environment and simultaneous assessments of the long-term evaluation of the mental, psychosocial, and QoL domains.

## Methods and design

### Study aims

The primary aim of this study is to identify whether or not there is any significant improvement in speech recognition in noise in older adults patients ( > = 65 years) who are using HA for the first time. This improvement is to be verified by using a Signal to Noise Ratio (SNR) reduction which will be evaluated using the OLSA test.The secondary aim is to process the correlations between the use of the HA and quality of life and cognitive status in older adults. Any improvement or deterioration can be seen in higher or lower scores in auto-assessment questionnaires.

### Study design

This is a prospective observational, repeated measurement, single-subject design study.

Changes in speech recognition by noise score, health-related quality of life, and overall well-being are assesses.

The study design is monocentric and is conducted at the outpatient service of the ENT Department of the “Saliceto” Hospital in Piacenza, Italy.

All the materials used are appropriate for the italian language.

This study is registered with the Ethics Committee of the Area Vasta Emilia Nord under number 104; date of approval 17/07/2017.

### Timing schedule

The study protocol assessments coincides with the routine clinical examinations. Full test-battery and questionnaires are administered in both examinations: one before the HA fitting (Pre) and the other after one year of HA use (Post).

A short description of the procedure is shown in Table 1 and listed below.

**Table 1 Tab1:** procedure and assessment tools used at different time of evaluation

	Enrolment	Post-allocation	
**TIMEPOINT**	***t***_***0***_	***Pre***	***Post***
**ENROLMENT**			
** Eligibility screen**	X		
**Informed consent**	X		
**Allocation**	X		
**AUDIOMETRIC ASSESSMENTS**			
***unaided pure tone audiometry***		X	X
***unaided speech audiometry***		X	
***aided speech audiometry***			X
***test of the HA functioning***			X
***OLSA test***		X	X
***SELF-ASSESSMENTS QUESTIONNAIRES***			
***MOCA***		X	X
***HHIE-S***		X	X
***AQoL***		X	X
***IOI-HA***			X

Baseline (t0):

Signature of the Patient giving Informed Consent..

First assessment (Pre):

otoscopy and cleaning of the external auditory canal (if required).unaided pure tone audiometry (right and left ear).unaided speech audiometry in quiet (right and left ear).Italian version of Oldenburg Satztest (OLSA test) [19].Self-assessment questionnaires:Montreal Cognitive Assessment (MoCA) [20].Hearing Handicap Inventory in the Elderly Screening test (HHIE-S) [21].Assessment of Quality of Life *(*AQoL) [22].Abbreviated Profile of Hearing *A*id Benefit (APHAB) [23]..

Second assessment (Post):

otoscopy and cleaning of the external auditory canal (if required).test of the HA functioning.unaided pure tone audiometry (right and left ear).aided speech audiometry in quiet (in free field).Italian version of OLSA test.Self-assessment questionnaires:

MoCA.HHIE-SAQoL.International Outcome Inventory for Hearing Aids (IOI-HA) [24].APHAB in aided condition.

To complete all the measures takes approximately one hour: 30 minutes for performing the standard self-report questionnaires and 30 minutes for the other tests.

### Subjects

Study subjects who use unilateral or bilateral hearing aids for the first time are to be included. Eligible participants are consecutively identified on the HA registry of the Local Unit of the National Health System (NHS). The Italian NHS is a welfare system which totally or partially funds the HA costs of the patients selected.

Subjects are > = 65 years old using unilateral or bilateral HA for the first time. According to local NHS threshold-criteria for funding adult HAs, the best ear of the patients must have a Pure-Tone Average (PTA) > = 45 dB HL. PTA is the average air-tonal threshold at 500, 1000, 2000, and 4000 Hz frequencies.

Only the subjects who signed the Patient Informed Consent Form prior to the first assessment (baseline, t0) are eligible for the clinical investigation.Approximately 100 individuals will be included. The sample size of 100 people was recruited according to a previous preliminary study by the authors (Tognola et al. 2019) and depending on olderpopulation eligible to utilize HA. Indeed, eligible participants are consecutively identified in the HA registry of the Local Unit of the National Health System (NHS).

#### Selection Criteria

Inclusion:

Age > = 65 years.First use of unilateral or bilateral HA.HA partially or totally funded by the Italian National Health System.Willingness to participate in.Willingness to comply with all study procedures.Fluency in italian language used to assess clinical performance.Able to decide on study participation personally.Able to independently sign their consent..

Exclusion:

Unilateral hearing loss.Previous use of HA.Significantly/severely dependent or fragile.Unable to provide consent personally.Unable to complete questionnaires for self-assessment independently.Significant comorbidities preventing study participation.Subjects with unrealistic expectations on benefits, risks and limitations concerning the procedure and prosthetic device..

### Materials

Changes in the hearing aid benefit and the overall health status of the older adults at post-HA use are evaluated by a selection of observational clinical assessment tools frequently used in audiology and/or geriatric practices.

All questionnaires have been validated for the Italian language.

Expert personnel have been designated to manage the administration of the questionnaires in order to understand whether or not the subject clearly understands what the task involves.

A short description of the administered assessments is listed alphabetically below (see Table 2).

**Table 2 Tab2:** Healthy-ageing domains and assessment tools used for evaluation

Domain	Clinician report	Self-report by recipient			Routine Audiology		
	MOCA	AQoL	IOI-HA	HHIE-S	PTA	SRT	OLSA Test
Hearing					◆	◆	◆
Emotional			◆	◆			
Cognition	◆						
Loneliness / Social Isolation			◆	◆			
General Health		◆	◆				
Quality of Life		◆	◆				

#### Abbreviated Profile of Hearing Aid Benefit (APHAB)

Abbreviated profile of Hearing Aid Benefit (APHAB) is the abbreviated version of the Profile of Hearing Aid Benefit (66 items).

APHAB is a self-assessment questionnaire composed of 24 questions that assess the advantage and the communicative problems of HA use [25].

The data obtained provides information about several typical workday situations considering four subscales: Ease of Communication, Reverberation, Background Noise, and Aversiveness of Sounds.

A low APHAB score indicates better performances. A measurement of the benefit will be calculated by subtracting APHAB scores in Post evaluation (with HA) from Pre evaluation.

The Italian translation of the APHAB questionnaire is available on the Hearing Aid Research Lab (HARL) web site at (https://harlmemphis.org/wp content/uploads/2020/05/ITALIAN.pdf) [23].

#### Assessment of Quality of Life (AQoL-8D)

The Assessment of Quality of Life (AQoL) was designed for use across health conditions to enable evaluation studies of health economics. AQoL assesses the impact of interventions on health-related quality of life by comparing different disease settings and monitoring longitudinal changes in a broad range of health conditions [26–28].

The AQoL-8D consists of five psychosocial and three physical dimensions. The three physical dimensions are related to a single construct (the ‘physical super-dimension’) and the five psychosocial dimensions are related to a single construct (the ‘mental super-dimension’).

The test includes 35 items with 5 possible answers.

The Italian translation of the AQoL questionnaire is available on the AQoL web site (www.aqol.com.au) [22].

#### Audiometric Assessments (Routine)

These include standard threshold measurements for frequencies of 250–8000 Hz (pure tone audiogram) and speech discrimination (speech audiometry) in a quiet situation. The pure tone audiometryis performed in a soundproof room using a Madsen Astera (by Natus Medical Incorporated, Denmark) audiometer and TDH39 supra-aural earphones.

The pure tone audiometryunder earphone is assessed in Pre and Post evaluations, and in unaided (dB HL) condition. Speech audiometry is assessed in Pre-evaluation under earphone whereas it is assessed in the free field in aided (dB SPL) condition in Post evaluation.

Speech audiometry shows the Speech Reception Threshold (SRT), defined as the level of speech corresponding to 50 % of correct answers. In the SRT test, the speech stimuli (list of disyllabic words) [29] are pre-recorded and delivered by a loudspeaker at zero degrees azimuth in the sound field.

The subject is asked to repeat a list of 20 words (phonetically balanced) and the percentage of correctly repeated words is evaluated for each intensity-level presented. The intensity ranges between 30 and 80 dB HL and every word list is presented at an intensity of 10 dB higher than the previous one. An intelligibility curve is obtained and SRT is derived by curve interpolation.

#### Hearing Handicap Inventory in the Elderly Screening test (HHIE-S)

The Hearing Handicap Inventory for the Elderly Screening Version (HHIE-S) is a self-assessment scale developed to assess the effects of hearing impairment on emotional and social adjustment in everyday life of the older adults [30–33].

This test contains a 10-item questionnaire. A low HHIE-S score indicates fewer perceived problems.

The Italian version of this material is under publication [21].

#### International Outcome Inventory for Hearing Aids (IOI-HA)

The International Outcome Inventory for Hearing Aids (IOI-HA) is a self-report questionnaire developed to quantify the satisfaction of hearing aid users and the impact these devices have on their lives. The IOI-HA contains seven domains:(1) the time for whichHAhave been used;(2) benefit; (3) residual limitation in daily life activities; (4) satisfaction; (5) residual restrictions to participation; (6) impact on other people; (7) quality of life. The answers to each question range from poor performance (1) to best performance (5) [34, 35].

A high score is correlated with a good outcome in aided conditions.

Cox et al. were responsible for the Italian validation of this questionnaire [24].

#### Montreal Cognitive Assessment (MoCA)

Montreal Cognitive Assessment (MoCA) is a cognitive screening instrument used to detect mild cognitive impairment, a high-risk condition for dementia forms [20, 36–38].

It is composed of 12 subtasks assessing different cognitive skills, including short-term and delayed verbal memory, executive function, and attention. The total MoCA score ranges from 0 (worst performance) to 30 (best performance). Mild cognitive dysfunction is suspected when the final score is less than 26.

Different strategies will be integrate by clinicians in order to avoid a misdiagnosis or overdiagnosis of cognitive impairment. Personnel will be trainedto administrationof this tool in patients with hearing loss. In particular, they will assess the correct use of hearing aids; they will ensure that the test environments meet standards for ambient noise levels and they can use alternative presentation modality of the items with auditorycontents (with multimodal presentation: both auditory and visual presentation) [39].Santangelo et al. produced the normative data for the Italian population [20].

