During this study two-time point, tonal unaided audiometry was used to check any auditory threshold modification and worsening of the audiometric clinical situation over time. Speech audiometry in unaided conditions in the first assessment and in aided conditions in the second assessment were used because it describes the sample and allows it to be compared to the existing literature.

The second objective of this study is based on the evaluation of possible improvements in the overall health-related quality of life in the sample.

To verify this aim, self-report questionnaires were chosen, which are essentially non-verbal and consequently remove challenges directly associated with utilizing new HA. The percentage of subjects who improve the questionnaire score using HA (second assessment) compared to the first evaluation in unaided conditions is to be evaluated.

Improvement in quality of life can be evaluated by using different questionnaires. The AQoL questionnaire is used in this study because of its robust psychometric characteristics and wide diffusion in the health-related quality of life literature. In a review by Mihalopoulos et al., (thatanalyzesinstruments for depression outcome measurements) report that AQoL-8D “had the highest correlation with the disease-specific measurements and the best goodness-of-fit transformation properties” [28].

The HHIE has been included in the study in order to better understand the effects of hearing impairment on emotional and social adjustment in everyday life. It is one of the most widely applied questionnaires with respect to auditory participation and has been reported with both HA and cochlear implant recipients [41]. A significant reduction of the questionnaire score in Post vs. Pre-evaluation is expected in this study, which suggests quality of life improvement.

The MoCA questionnaire was chosen to screen the cognitive abilities of subjects. The use of this questionnaire will exclude deficits in these abilities. Using this test in Pre and Post evaluation will verify that cognitive abilities do not affect other questionnaires and HA results. The use of the MoCA questionnaire in the Pre and Post evaluation will exclude a reduction of the cognitive abilities over time. A reduction of these abilities can be a sign of the deterioration of the general state of health that may affect the execution of the other questionnaires used. The same score is expected in Pre and Post evaluation of the same subject.

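### MoCA is taken unaided at Pre and apparently aided at Post, with optional visual presentation, so neither a changed nor an unchanged score can be cleanly attributed to cognition

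*Protocol article*

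**What the plan says.** All of this is in the protocol article.

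- **Timing.** Table 1 and the list under Timing schedule place MoCA at both assessments, "one before the HA fitting (Pre) and the other after one year of HA use (Post").
- **Population.** Selection Criteria exclude "Previous use of HA". Under Subjects, "the best ear of the patients must have a Pure-Tone Average (PTA") of 45 dB HL or more.
- **Safeguards.** The MoCA section aims to avoid wrong or excess diagnosis of impairment in people with hearing loss. Staff are trained, "they will assess the correct use of hearing aids", and ambient noise is controlled. For combined auditory and visual presentation the verb changes: "they can use alternative presentation modality of the items with auditorycontents".
- **Condition at each visit.** The Discussion describes the questionnaire comparison as "using HA (second assessment) compared to the first evaluation in unaided conditions". The Timing schedule lists "test of the HA functioning" for the second assessment only.
- **Use of the score.** Cognitive status is part of the secondary aim (Study aims). Within-subject Pre-Post comparison applies to primary and secondary objectives (Statistical considerations). The Discussion uses the two MoCA scores to rule out cognitive decline over the year and to show that cognition does not affect the other results. It adds: "The same score is expected in Pre and Post evaluation of the same subject".

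**The concern.** The MoCA section itself acknowledges that some items have auditory content. A person with this degree of hearing loss can lose points by not hearing an item as well as by failing it. If the same person hears better at one visit than at the other, the difference between the scores mixes audibility with cognition.

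Two readings of the score are at stake. The first is the control reading in the Discussion, where a stable MoCA is taken to show that cognition did not decline. An audibility gain at Post could offset a true fall and leave the score unchanged. The second is the cognitive part of the secondary aim, where a rise could partly be a hearing effect. If MoCA enters the planned factor analysis, correlations and regression, it carries the same mixture there.

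**Working it through.** The plan states no figure for the MoCA change, and its sample size of about 100 comes without an effect size or SD for MoCA, so there is nothing of its own to reproduce. The main check is to set the passages side by side.

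**Step 1: aided status at Pre.** Pre precedes fitting and earlier users are excluded, so no subject has an own aid. Unaided testing at Pre follows from the design.

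**Step 2: aided status at Post.** No sentence about MoCA alone says that aids are worn. The inference rests on two places: the MoCA section has staff check correct aid use, which can apply only at Post, and the Discussion contrasts aided and unaided conditions for the questionnaires, with which Table 1 groups MoCA. The inference is strong, but it remains an inference.

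**Step 3: which safeguards equalise the visits?**

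| Safeguard | Pre | Post | Equalises audibility? |
|---|---|---|---|
| Check of correct aid use | cannot operate | operates | No, it widens the difference |
| Ambient-noise control | yes | yes | No, it does not restore hearing to an unaided listener |
| Trained staff | yes | yes | Not by itself; no rule fixes the mode |
| Combined auditory and visual items | optional | optional | Only if used alike at both visits, which is not required |

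**Step 4: illustration of size.** The inputs below are assumptions, except the 100 subjects.

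- n = 100 pairs (all of the approximately 100 planned subjects, no dropout)
- two-sided alpha 0.05, critical value 1.96
- no true cognitive change
- audibility shift d of 0.5 or 1 point
- SD of the within-subject change, s, of 2, 3 or 4 points

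Formula (normal approximation, paired comparison):

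P(significant) = Φ(d√n/s − 1.96) + Φ(−d√n/s − 1.96)

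Worked example for d = 0.5, s = 4: d√n/s = 0.5 × 10/4 = 1.25, and Φ(−0.71) + Φ(−3.21) ≈ 0.24.

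| Shift d | s = 2 | s = 3 | s = 4 |
|---|---|---|---|
| 0.5 point | 0.705 | 0.385 | 0.240 |
| 1 point | 0.999 | 0.915 | 0.705 |

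Statistical considerations assigns questionnaires a nonparametric test. A simulated Wilcoxon signed-rank test at d = 1 gives similar values: over 0.99 at s = 2 and about 0.9 at s = 3.

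**Step 5: masking.** If true cognition falls by 1 point and audibility adds 1 point, the expected change is −1 + 1 = 0. The chance of detecting the decline drops from 0.999, 0.915 or 0.705 (s = 2, 3, 4) to the false-positive rate of 0.05.

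**The case against.** A reader might go further and infer that better hearing will be reported as cognitive benefit. The documents do not support that. The Discussion gives MoCA a screening and control role, expects no change and disclaims causal investigation. The Study aims sentence on higher and lower scores concerns self-assessment questionnaires. Table 1 lists MoCA among these, while Table 2 classes it as clinician-reported, so that link is ambiguous. The accurate wording is that a change can be misread, and masked decline is the reading with the firmest basis in the text.

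Direction is open as well. Given the stated purpose of avoiding misdiagnosis, staff may use visual support most at Pre, when no aid is worn. That would shrink or even reverse the artefact. Nor should one infer that the score of 26 adds to the damage: it appears only as the instrument's screening threshold, not as an eligibility rule, endpoint or analysis category.

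The size is assumed, and with a fixed 1-point shift and a small SD a high probability is built in. For that reason the full range is shown above.

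Finally, this is a condensed article, and item-level instructions may sit in a manual. That holds for which items are shown and how. It does not remove the point, because the article itself makes the aid check and noise control firm and leaves the equalising measure optional, while relying on the comparison between visits.

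**Conclusion.** The point holds as a measurement problem on a secondary outcome. As written, the plan lets presentation mode vary between visits and, by design and inference, has aided status differ. The Pre-Post MoCA comparison is therefore confounded with audibility. A changed score cannot be assigned to cognition, and an unchanged one does not exclude decline.

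The documents fix neither the sign nor the size of the bias. Under the assumptions shown, the chance that audibility alone produces a significant result runs from about 0.24 to over 0.99. This range shows that a modest artefact could matter with about 100 subjects; it does not estimate the artefact. If combined presentation is in fact used for everyone at both visits, the bias shrinks, but the text does not require it. The primary endpoint, speech recognition in noise, is not touched by this point.

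**What to change.** 1. For subjects not yet tested at Pre, require combined auditory and visual presentation of all auditory MoCA items at both visits.
2. For subjects already tested at Pre, use at Post the same mode as at Pre where it is known. Imposing the combined mode at Post on someone tested by ear alone at Pre would create the very mismatch at issue.
3. Record presentation mode and aided status on the form at each visit.
4. Base the Pre-Post MoCA comparison on same-mode pairs. Because aided status still differs within those pairs, add a sensitivity analysis that leaves out the auditory-dependent items.
5. Do not interpret the change as cognition where the mode differs or is unknown.

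The combined method is already foreseen, so for new subjects the cost is an instruction to testers, two form entries per visit and slightly less comparability with purely auditory MoCA norms. Among subjects already tested there will be fewer usable pairs, because the Pre mode may not have been recorded and a Pre test cannot be repeated once the subject has become an experienced user.
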